### Interventions

2.6

#### The eHealth ecosystem, ICOnnecta't

2.6.1

ICOnnecta't is a stepped-care psychosocial intervention that comprises four levels staggered by psychosocial complexity (see Fig. 2). In this way, it aims to provide progressively adjusted psychosocial care starting with the least intensive and complex intervention first (Hutchison et al., 2006). Through the systematic monitoring of specific clinical variables (Level 1, i.e., emotional distress), the patient's psychosocial status can be established to decide whether they should move to a more intensive and complex step (Lutz, 2003). The intervention levels of ICOnnecta't are based on those of other published interventions that use a stepped approach, and they aim to manage emotional distress in the cancer population. Four levels of care are usual: that range from basic psychoeducation (ICOnnecta't level 2) to intensive psychotherapy (ICOnnecta't level 4) (Braamse et al., 2016; Butow et al., 2015; Hauffman et al., 2020; Hutchison et al., 2006; Krebber et al., 2016; Kusch et al., 2022; Rissanen et al., 2015). Some authors recommend incorporating peer support communities into stepped interventions to promote wellness, self-care habits, and connectedness (Butow et al., 2015; Hauffman et al., 2020; Hutchison et al., 2006; Ramchand et al., 2017).

All patients will join the program at level 1 and, each time they step up, will retain access to the previous step (Chan et al., 2013). All patient journeys in the stepped intervention will be guided by a lead health psychologist with expertise in psycho-oncology. Patients can be referred to psycho-oncology, psychiatry, or social work departments, as necessary. The detailed interventions at each level, together with the escalation protocol, are based and adapted on the protocol used for breast cancer (Ochoa-Arnedo et al., 2020), and these are detailed below.

##### Level 1: screening and monitoring

2.6.1.1

Screening of potential emotional distress and monitoring of physical symptoms through a mobile application (ICOnnecta't App). Patients can spontaneously communicate their mood through a VAS emotional thermometer. In addition, a health psychologist will program a weekly assessment with the same thermometer, with a score ≥ 6 (10 indicating maximum distress) triggering a video consultation or phone call to assess the distress and explore any specific psychosocial needs. These sessions are also intended to accompany the patient throughout their cancer journey. Before a session, patients complete the HADS, and if both the HADS (≥ 10) and the psychologist's impression confirm clinically significant distress, the patient will be escalated to the next level. This adaptation of a stepped-care program used in oncology will be followed for escalation to the subsequent levels (Jansen et al., 2017).

##### Level 2: campus: psychoeducation and health education

2.6.1.2

The ICOnnecta't Campus is an educational platform that can be accessed via Moodle. It allows patients to consult videos and online resources developed by health professionals and based on patient feedback. The campus therefore contains scientifically validated information related to the diagnosis and treatment of advanced oncological disease, organized into different thematic blocks that represent the usual challenges involved with an advanced oncological diagnosis (Graves et al., 2007). The key areas are as follows: (a) The medical aspects of lung cancer in 14 resources (i.e., common symptoms, medical treatments, and side effects; (b) Emotional aspects, with eight resources about emotional responses to diagnoses and treatment; (c) Personal relationships, with four resources addressed to family members and caregivers about the role of the family in treatment and how they can aid the patient during the process; d) Healthy habits, comprising 28 resources about exercise, healthy eating models, rest and self-care; and e) Spiritual, comprising three resources about spiritual worries, shared decision-making, and advance directives. The patient will remain at this level for two weeks. If distress does not decrease on the thermometer (score ≥ 6), a HADS and video consultation or phone call will be scheduled to assess the appropriateness (HADS score ≥ 10) of moving to the next level of care.

##### Level 3: community psychosocial support

2.6.1.3

The service provides a safe online community where patients can anonymously share potential concerns related to the oncological process, resolve doubts and health issues, share experiences, or discuss issues related to the disease. This private social network contains several discussion forums related to advanced lung cancer and its possible implications, and they parallel the thematic blocks of ICOnnecta't Campus (level 2). It is supervised by a health psychologist who will provide a professional response with the support of other specialist members of the oncology team (e.g., psycho-oncologist, nurse, psychiatrist, and social worker). As in the previous level, the patient remains in this level for two weeks and is only advanced to level 4 if distress remains high (thermometer score ≥ 6), and a subsequent HADS score, and video or phone consultation indicate this is appropriate.

##### Level 4: online group psychotherapy

2.6.1.4

In the final level, patients are offered online group psychotherapy led by a clinical psychologist with expertise in psycho-oncology. This comprises eight weekly 90-min sessions that use the meaning-centered group psychotherapy approach developed by Breitbart et al. (2015). Patients at this level remain on a waiting list until four to eight users become available for the group sessions.

#### Treatment as usual - psychosocial face-to-face treatment

2.6.2

Patients in the control group will receive standard in-person psychosocial care delivered by a clinical psychologist. This will consist of an average of seven individual sessions, lasting 45–60 min each, with an inter-session spacing of 2–3 weeks. The clinical psychologist will provide the intervention based on individual meaning-centered psychotherapy for advanced cancer patients (Breitbart et al., 2012), aiming to help maintain or enhance the sense of meaning, peace, and purpose in the lives of patients with advanced cancer. Patients in this treatment arm will also have access to the educational materials of level 2 of the eHealth intervention, which will be provided in a freely accessible web portal for all patients and their families.

### Power analysis

2.7

The sample size has been estimated using R software, setting a non-inferiority margin of 5 points on the HADS (Vaganian et al., 2020) with a power of 80 % and a one-tailed α of 2.5 %. Assuming a dropout rate of 25 %, we require 152 participants (76 per branch) to ensure a 95 % bilateral confidence interval that excludes the non-inferiority threshold.

### Data protection and ethics compliance

2.8

Two databases will be created. The first will turn participants' personal identification data (e.g., names, patient ID) into an alphanumeric code that will be saved on an external hard drive and stored in a locked cabinet within the principal investigator's office. The second will use these alphanumeric codes to record all data collected for analysis, and it will be stored in a REDCap repository compliant with the General Data Protection Regulation. This procedure allows us to perform the anonymous analysis. The data will be downloaded monthly from the online questionnaire system used for the evaluations, coded in both databases, and backed up on a second encrypted external hard drive.

### Planned statistical analysis

2.9

Descriptive analyses will be performed using Student t or chi-squared tests, as appropriate. This will include assessment of sociodemographic and clinical variables at baseline, together with any pre-treatment differences between groups. Intention-to-treat analyses will then be performed through multilevel linear models to compare both groups on each primary outcome: emotional distress (HADS), demoralization (DS-II), QoL (FACT-L), and medication adherence (ARMS-e).

The modeling process will be parsimonious and guided by fit indexes, starting with a model using the time and type of therapy as fixed predictors. Then, random effects will be tested, and the interaction between time and type of therapy, the eHealth step reached, symptomatology (ESAS-r), and spirituality (FACIT-Sp) will be progressively entered as predictors. The estimation method will be maximum likelihood. Effect sizes (Hedges' g) will be reported for the primary outcomes and non-inferiority will be assessed for the HADS by comparing the means of both groups at T2 and T3. Additional multilevel linear models will be run to assess changes in health education (VAS) between groups, according to the same procedures. As for the cost-utility analyses, the EQ-5D will be used to compute the QALYs together with associated costs for medical care, psychotropics, sick leave, professional salaries, infrastructure, and transportation.

Descriptive analyses will also be conducted for platform's satisfaction and usability (VAS), as well as for participants reaching each step in the eHealth group. Mean differences in the number of clinical cases detected (according to the emotional thermometer), waiting time to provide care, and number of clinical cases solved will then be compared between groups by Student *t*-tests. For the reporting of results, 95 % confidence intervals will be provided. Analyses will be performed using IBM SPSS version 24 (IBM Corp., Armonk, NY, USA) and R software, with support provided by the biostatistics department of IDIBELL.

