### Study design

2.1

This study proposes a randomized non-inferiority trial of an eHealth ecosystem compared to usual psychosocial care. The main outcomes will be assessed at baseline (T0), 3 months from T0 (T1), 6 months from T0 (T2), and 9 months from T0 (T3). Therefore, the design comprises two treatment conditions and four assessments. We chose the non-inferiority based on a literature review that indicated mixed and inconsistent results when comparing eHealth and face-to-face psychosocial interventions in cancer (Merluzzi et al., 2019; Singleton et al., 2022; Wang et al., 2020; Xu et al., 2019). Therefore, we do not hypothesize that our eHealth ecosystem will be more efficacious than usual care, but instead, aim to show that it is at least not inferior in terms of efficacy and efficiency. The methodology will adhere to the principles of Responsible Research and Innovation (RRI, European Commission, Directorate-General for Communication, 2013).

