### Timeline

2.4

At the baseline visit, researchers will explain the study and obtain informed signed consent. They will then introduce the patient to REDCap, a secure web platform for building and managing online databases and surveys (https://www.project-redcap.org/). After checking eligibility at baseline, patients will be randomly allocated to one of the two treatment arms by REDCap, using simple randomization. The clinician-administered face-to-face questionnaires will be administered to all patients at this baseline evaluation (T0), while REDCap will send self-administered measures by e-mail at baseline (T0), 3 months (T1), 6 months (T2), and 9 months (T3) (Fig. 1).

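### Fit indexes choose the fixed effects of the between-arm models and may drop time-by-therapy, which would shrink the arm effect toward zero; whether this reaches the HADS non-inferiority verdict is left open

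*Protocol article*

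**What the plan says.** Section 2.9 (Planned statistical analysis) uses multilevel linear models for the intention-to-treat comparison of the arms on HADS, DS-II, FACT-L and ARMS-e. It sets the rule for choosing the model: "The modeling process will be parsimonious and guided by fit indexes, starting with a model using the time and type of therapy as fixed predictors". Random effects are tested next, and then "the interaction between time and type of therapy, the eHealth step reached, symptomatology (ESAS-r), and spirituality (FACIT-Sp) will be progressively entered as predictors". On estimation it says "The estimation method will be maximum likelihood". No fit index is named, no term is declared fixed, and no adjustment for the baseline score is described.

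The same section has a separate sentence on non-inferiority: "non-inferiority will be assessed for the HADS by comparing the means of both groups at T2 and T3". It does not say whether these are observed means or means estimated from the multilevel model.

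Section 2.1 says "the design comprises two treatment conditions and four assessments", the first assessment being baseline (T0). Section 2.4 says that "patients will be randomly allocated to one of the two treatment arms by REDCap, using simple randomization". Section 2.7 describes the sample size as "setting a non-inferiority margin of 5 points on the HADS", with 80% power, one-sided α of 2.5%, 25% dropout and 76 patients per arm.

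**The concern.** In a longitudinal model with T0 among the outcomes, the treatment effect lies in the time-by-therapy interaction. At T0 the expected difference between randomised arms is zero, and any effect appears afterwards. A model with time and therapy as main effects only forces one common difference on all four visits, so its arm coefficient is a blend that includes the zero at T0.

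The selection rule starts from that model and favours parsimony. A modest but real effect is the kind of signal that a penalised fit index can discard. The shrinkage is always toward zero. In a superiority setting that costs power; in a non-inferiority setting it makes a worse treatment look closer to the comparator. A confidence interval computed after selection also takes no account of the selection.

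This is not a detail left for a later document. The article states a rule for the confirmatory fixed effects, and that rule does not protect the term that matters.

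**Working it through.** **Inputs.** From the article: margin 5 HADS points, one-sided α 2.5%, power 80%, 76 per arm, 25% dropout, visits T0–T3. Assumed, because the article does not give them: SD of the HADS total, within-patient correlation, the pattern of true differences over time, T0 as a modelled outcome, and the fit index.

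**Step 1. The plan's own sample size.** With a true difference of 0, n per arm = 2 × SD² × (1.96 + 0.8416)² / 5². SD 9.5 gives 2 × 90.25 × 7.849 / 25 = 56.7, so 57; and 57 / 0.75 = 76. The stated 76 is attainable, but SD 9.5 is back-solved, not verified. With a true difference of 1 the implied SD is about 7.6.

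**Step 2. Dilution.** With balanced data and a random intercept, the main-effects arm estimate is the mean of the four visit differences.
- Step pattern: (0 + 5 + 5 + 5) / 4 = 3.75, a shrinkage of 25%.
- Ramp pattern: (0 + 1.67 + 3.33 + 5) / 4 = 2.5, a shrinkage of 50%.

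Model-based differences at T2 and T3 from such a model are identical, and both equal this average.

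**Step 3. False non-inferiority if the main-effects model is kept and used for the verdict.** SE = SD × √[((1 + 3ρ)/4) × (2/57)]. With SD 9.5 and ρ = 0.6, SE = 9.5 × √(0.7 × 0.03509) = 1.489. The success probability is Φ[(5 − mean difference)/SE − 1.96].
- Step: 1.25/1.489 − 1.96 = −1.12, giving 13.1%.
- Ramp: 2.5/1.489 − 1.96 = −0.28, giving 38.9%.

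**Step 4. With the selection step included.** Simulation of the same model: 6,000 runs, 57 per arm, SD 9.5, correlation 0.6, categorical time, true T3 difference 5.

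| Rule for the interaction | Step | Ramp |
|---|---|---|
| Always kept, contrast at T3 | about 2.5% | about 2.5% |
| AIC decides | about 3% | about 6% |
| BIC decides | about 8% | about 29% |
| Never entered (closed form) | 13.1% | 38.9% |

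BIC kept the interaction in only about 42% (step) and 24% (ramp) of runs.

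**Step 5. Range over the assumptions.** For SD 7 to 9.5 and correlation 0.5 to 0.7:
- Main-effects model kept: 12.3% to 22.5% (step) and 35.8% to 67.4% (ramp).
- Categorical time: AIC 2.3% to 9.0%, BIC 2.8% to 37%.
- Linear time: AIC 0.3% to 4.2%, BIC 0.6% to 14%. Values below nominal arise because a straight line fitted to the step pattern overstates T3: the slope is 1.5 per visit, so the fitted T3 difference is 3.75 + 1.5 × 1.5 = 6.0.

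The simulation treats the 57 per arm as complete and models no further dropout.

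**Step 6. Raw means.** A direct comparison of observed means at T3 does not involve T0. With a true difference equal to the margin, its error is 2.5%.

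**The case against.** The strongest objection is the article's own non-inferiority sentence. It compares HADS means at T2 and T3; it does not make the arm coefficient the basis of the verdict, and T0 is not in the comparison. If the means are observed ones, there is no dilution. This stands. A reader might infer from the modelling rule that the HADS verdict itself is biased toward non-inferiority, but the text does not support that. What remains is that the sentence follows directly on the multilevel models and does not say which means it intends.

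Second, the main-effects model is only the start, and the interaction is an explicit candidate. That is true, and it is why the figures for a main-effects model that is kept are a conditional worst case. Under AIC the error stays near nominal in most settings. The large figures need BIC or a similarly strict criterion, and the article names none.

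Third, T0 as a modelled outcome is inferred from four assessments, a time predictor and no described baseline adjustment. The inference is reasonable, but it is not a statement in the text.

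Fourth, a reader might extend the inflated non-inferiority error to DS-II, FACT-L and ARMS-e. That does not follow: the margin in section 2.7 and the assessment in section 2.9 concern the HADS only. For these three outcomes the problem is a diluted estimate, although section 1.1 does hypothesise equivalence to usual care on them.

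Finally, a condensed article may leave the full model to another document. That would excuse silence, but here the article states a selection rule.

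**Conclusion.** The point holds in a limited form. The rule in section 2.9 lets fit and parsimony decide whether the time-by-therapy term survives. If T0 is a modelled outcome and the term is dropped, the arm effect shrinks by 25% (step) or 50% (ramp). The model-based comparisons of DS-II, FACT-L and ARMS-e are exposed to this directly, as estimates.

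For the HADS verdict the exposure is conditional: the T2 and T3 means must come from a selected model without the interaction. On that reading, and with the assumed SD 9.5, correlation 0.6 and categorical time, false non-inferiority lies between about 3% and 29% depending on the index, and reaches 13% or 39% if the main-effects model is simply kept. The mechanism is certain. Its size rests on inputs that the article does not give, and its reach to the HADS verdict rests on wording that the article leaves open. It should be corrected before analysis, but it does not show that the planned non-inferiority test is invalid.

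**What to change.** Pre-specify one model for each of HADS, DS-II, FACT-L and ARMS-e, with arm, categorical time and arm-by-time always retained. Handle baseline in either of two acceptable ways: as a covariate with T1–T3 as outcomes, or as one of the outcomes with arm-by-time kept. State that the HADS contrasts at T2 and T3, with their 95% confidence intervals, come from this model. Use fit indexes only to choose the random-effects or covariance structure, and name the index. The other candidate predictors can go into separate explanatory models that do not feed the arm comparison.

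The cost is analysis wording and a few degrees of freedom. Recruitment, visits and data collection do not change.

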#### Primary outcomes

2.5.1

Hospital Anxiety and Depression Scale (HADS): Assessed emotional distress through 7 anxiety items (HADS-Anxiety) and 7 depression items (HADS-Depression). The range of scores is 0–21 for each subscale, and 0–42 for the overall questionnaire. An overall score ≥ 10 is indicative of moderate emotional distress and ≥ 16 of high emotional distress (Carmen Terol-Cantero et al., 2015).

Functional Assessment of Chronic Illness Therapy-Spiritual Well-Being (FACIT-Sp): Spirituality will be assessed through the Spanish version of the FACIT-Sp (Peterman et al., 2002). This instrument assesses three dimensions of spirituality through two subscales: 1) meaning and peace (8 items), and 2) faith (4 items). The overall score ranges between 0 and 48, between 0 and 32 for the first subscale, and 16 for the second. Higher scores are indicative of greater spiritual well-being.

Demoralization Scale – abbreviated version (DS-II): Patient's demoralization will be assessed through the Spanish version of DS-II (Belar et al., 2019). The DS-II is composed of 16 items, 8 for each of its two subscales: 1) meaning and purpose, and 2) coping. Scores <10 indicate no demoralization, between 10 and 19 moderate demoralization, and > 20 severe demoralization.

Functional Assessment of Cancer Therapy – Lung Cancer (FACT-L): to measure the QoL of LC patients, the Spanish adaptation of the FACT-L will be used (Cella et al., 1998). The FACT-L is an instrument derived from the general cancer QoL questionnaire, FACT-G, with an added subscale specific to LC and its symptoms. It has 36 items organized into 5 subscales: 1) physical well-being, 2) functional well-being, 3) social/family well-being, 4) emotional well-being and 5) LC. Higher scores correspond to a better QoL.

Adherence to Refill and Medication Scale (ARMS-e): Medication adherence will be assessed trough the Spanish version (González-Bueno et al., 2017) of ARMS-e, which is a valid and reliable scale for patients with a chronic disease. This instrument consists of 12 questions: 8 are focused on the patient's consistency in taking medication appropriately and 4 on their proper collection. Lower overall scores correspond to better adherence.

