#### Secondary outcomes

2.5.2

Edmonton Symptom Assessment System (ESAS-r): Patients' symptomatology will be controlled through ESAS in its revised version, adapted and validated in Spanish (ESAS-r) (Carvajal et al., 2013). ESAS-r is an instrument that is commonly used both in palliative care and in advanced cancer situations. It has 10 visual numerical scales that assess physical and psychological symptoms. Higher scores are indicative of higher pain/distress. The burden and severity of symptoms may affect other variables analyzed in the study and.

Health education: will be assessed using a visual analogue scale (VAS, 0–10) scoring patients' satisfaction with the health information received during their cancer journey, both physically and emotionally.

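### Models labelled intention-to-treat take in the eHealth step reached, a one-arm variable set by distress after randomisation, so they stop estimating the randomised effect

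*Protocol article*

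**What the plan says.** Section 2.9 (Planned statistical analysis) announces intention-to-treat multilevel linear models comparing the groups on HADS, DS-II, FACT-L and ARMS-e. Modelling starts with time and therapy, tests random effects, and then "the interaction between time and type of therapy, the eHealth step reached, symptomatology (ESAS-r), and spirituality (FACIT-Sp) will be progressively entered as predictors". Fit indexes guide the choice. Non-inferiority is to be judged on HADS by comparing group means at T2 and T3. The section does not say which model, if any, supplies those means.

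Sections 2.6.1.1 to 2.6.1.3 define how a step is reached. At level 1 a thermometer score of 6 or more triggers a consultation. If HADS is at least 10 and the psychologist's impression agrees, "the patient will be escalated to the next level". The moves to levels 3 and 4 again depend on the thermometer, HADS and a consultation. Controls have no steps.

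Section 2.5.1 lists spirituality among the primary outcomes: "Spirituality will be assessed through the Spanish version of the FACIT-Sp". Section 2.5.2 lists ESAS-r as a secondary outcome and remarks: "The burden and severity of symptoms may affect other variables analyzed in the study". Section 2.4 has self-report measures sent at T0, T1, T2 and T3. The hypotheses in section 1.1 consider both baseline spirituality and its increase through the interventions as predictors of outcome.

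**The concern.** An intention-to-treat contrast compares everyone randomised to one arm with everyone randomised to the other. Step reached breaks that contrast in three ways: it is a consequence of allocation, it has no counterpart among controls, and it is partly built from HADS, the outcome on which non-inferiority is tested. With step in the model, the therapy coefficient compares controls, at whatever code they are given, with eHealth patients at (or extrapolated to) that same code. If controls share the code of level 1, the comparison is of all controls with eHealth patients who were never escalated, a group selected for low distress.

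Selection by fit adds to the problem. A variable derived from HADS will tend to improve the fit of a HADS model and so be kept.

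ESAS-r and FACIT-Sp are a conditional case. Follow-up values can be changed by either treatment, so adjusting for them can remove or distort part of the effect. T0 values cannot be changed by treatment and would be legitimate covariates.

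At stake are the declared between-arm results for four primary outcomes and, if the non-inferiority means come from an adjusted model, the trial's main conclusion.

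**Working it through.** **1. The plan's own figure.** Section 2.7 works by "setting a non-inferiority margin of 5 points on the HADS", "with a power of 80 % and a one-tailed α of 2.5" per cent. It adds: "Assuming a dropout rate of 25" per cent. It states no SD. Assuming a true difference of 0, n per arm = 2·SD²·(1.96 + 0.84)²/5². With SD = 9.5 this gives 57, and 57/0.75 = 76 per arm, the planned number. The SD of 9.5 is back-solved, so this shows consistency and is not an independent reproduction. I use SD 6 to 9.5 below.

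**2. Shift caused by step reached.** Take a single-visit linear model as a stand-in for the multilevel model. Controls have a constant step code c, so the step slope b comes from the eHealth arm alone:

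- b = r·SD(HADS)/SD(step), with r the within-arm correlation of step with HADS
- adjusted arm effect = raw arm difference − b·(mean step − c)

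The documents give neither r, nor the spread of steps, nor c. Assumed shares at levels 1 to 4:

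| Shares (%) | Mean step | SD(step) |
|---|---|---|
| 70/15/10/5 | 1.50 | 0.866 |
| 50/25/15/10 | 1.85 | 1.014 |
| 25/25/25/25 | 2.50 | 1.118 |

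Example: 50/25/15/10, SD 7.5, r = 0.5 gives b = 0.5 × 7.5/1.014 = 3.70. With c = 0 the shift is −3.70 × 1.85 = −6.8; with c = 1 it is −3.70 × 0.85 = −3.1.

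Shift in HADS points at a true difference of 0 (negative favours eHealth), over all three distributions and SD 6 to 9.5:

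| r | Controls coded 0 | Controls coded 1 |
|---|---|---|
| 0.1 | −1.0 to −2.1 | −0.35 to −1.3 |
| 0.3 | −3.1 to −6.4 | −1.0 to −3.8 |
| 0.5 | −5.2 to −10.6 | −1.7 to −6.4 |
| 0.7 | −7.3 to −14.9 | −2.4 to −8.9 |

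A least-squares check on 400,000 simulated patients (SD 7.5, a latent correlation of 0.5, 50/25/15/10) gave −6.0 with code 0, −2.8 with code 1, and about 0 without step.

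**3. Dependence on the escalation rule.** A second simulation took mean HADS 12, SD 7 to 9.5, between-visit correlation 0.6, 200,000 per arm and controls at the lowest step. Escalation was to step 2 on HADS ≥ 10 at T1 and to step 3 on HADS ≥ 10 at both T1 and T2.

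- All eligible patients escalated: a true zero becomes about −4.2 to −5.1.
- Half escalated: about −1.1 to −1.3.
- A quarter escalated: about −0.5.
- Half escalated, SD 7, each step lowering HADS by 2 points: a true deficit of about 3.7 becomes about 4.0, so the shift is against eHealth.

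**4. Shift caused by follow-up ESAS-r or FACIT-Sp.** Size = |r|·SD(HADS)·δ, with δ the arm difference on the covariate in SD units. For |r| 0.3 to 0.7 and SD 6 to 9.5:

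- δ = 0 gives no shift
- δ = 0.2 to 0.5 gives 0.4 to 3.3 points
- a 5-point shift needs δ of 0.75 to 2.8

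**5. What a shift would do to the non-inferiority test, if that test used the adjusted estimate.** At a true deficit equal to the margin, the chance of wrongly declaring non-inferiority is Φ(shift/SE − 1.96), with SE = SD·√(2/57), ignoring any change in SE from the adjustment. For a 2-point shift towards eHealth:

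- SD 9.5: SE = 1.78, and Φ(1.12 − 1.96) is about 20%
- SD 7: SE = 1.31, and Φ(1.53 − 1.96) is about 33%

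The nominal figure is 2.5%.

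**The case against.** Four stronger readings are tempting, and the documents support none of them.

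- *The bias exceeds the margin.* The article gives no HADS SD, step distribution, correlation or coding for controls. The calculated shift lies on either side of 5 points, and it is about 1 point if half of eligible patients are escalated. That is a realistic possibility, because escalation also needs a raised thermometer score and the psychologist's agreement.
- *The bias always favours eHealth.* That is the expected direction from the escalation rule, but effective higher steps can offset or reverse it. For ESAS-r and FACIT-Sp the direction depends on which arm they favour.
- *The non-inferiority verdict is compromised.* The test is described separately as a comparison of means at T2 and T3, and the model sequence starts with time and therapy only. The means may be unadjusted, and an analysis plan that is not shown may settle this.
- *ESAS-r and FACIT-Sp are post-baseline covariates.* Section 2.9 does not say so, and T0 values would do no harm.

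It is also fair to say that progressive entry of predictors can serve the stated hypothesis about spirituality.

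All of this limits size, direction and reach. It does not rescue step reached. That variable cannot be a baseline value, and it is named as a predictor in models presented as intention-to-treat comparisons. An explanatory aim justifies a separate model, which the text does not provide.

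**Conclusion.** Wrong as written. Any model containing step reached does not estimate the randomised between-arm effect, on HADS or on the other three modelled outcomes. This follows from the escalation rules and needs no numerical assumption.

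The size is not determined by the documents. Under the assumed inputs the HADS shift at a true difference of 0 runs from −0.35 to −14.9 points, so it may be negligible or larger than the margin. The expected direction is towards eHealth, provided that the higher steps do not lower distress enough to offset it.

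Two parts are conditional. ESAS-r and FACIT-Sp distort the effect only if follow-up values enter. The non-inferiority conclusion is affected only if the T2 and T3 means come from an adjusted model. The text leaves both open.

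**What to change.** State in section 2.9 that the primary between-arm estimates, and the HADS non-inferiority estimate at T2 and T3, come from one pre-specified model with therapy, time, their interaction and T0 covariates only, not chosen by fit. T0 values of ESAS-r and FACIT-Sp may be included.

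Remove step reached and post-baseline ESAS-r and FACIT-Sp from these models. Report step reached descriptively or in exploratory models within the eHealth arm. Examine follow-up symptoms and spirituality as outcomes, in exploratory models, or in a separate mediation analysis, which would still address the spirituality hypothesis.

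The cost is a change of wording. No new data, visits or patients are needed.
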